### Trial design

2.1

This prospective study was conducted using a parallel-group design with two groups. In the experimental group, the optimized communication protocol was applied (OPT), whereas the standard-of-care group (SOC) received communication according to a control protocol that uses standard communication observed in the clinic with no particular consideration of the effects of communication. The required sample size for the planned analysis of the main outcome (i.e., complete datasets from t1 to t5) was N = 80 inpatients, recruited in the general wards of the Neurology Department at the University Hospital Essen, with a balanced 1:1 group allocation ratio (n = 40 for SOC, n = 40 for OPT). The study was preregistered at the German Clinical Trials Register (DRKS00032272). This study protocol aligns with the SPIRIT guidelines (Standard Protocol Items: Recommendations for Interventional Trials) and follows the SPIRIT-PRO extension for patient-reported outcomes, as specified in Supplementary Table S1 (Chan et al., 2013; Calvert et al., 2018).

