### Sample size, randomization, and blinding

2.7

The sample size of N = 80 for the final analysis was chosen for reasons of feasibility while ensuring sufficient power to detect a clinically meaningful effect. With a power of 0.90, the study can detect an effect size f of at least 0.16 for the interaction effect between the group and time point on the primary outcome measure (headache-related impairment) (G*Power 3.1.9.7). This corresponds to a small to medium effect size. The recruitment period was set at 6 months (December 2023–May 2024), based on predetermined staff resources and estimates of the expected number of eligible study patients from recruitment from the wards. This timeline was expected to yield an effective sample size of 80 participants, accounting for an anticipated attrition rate of 15%.

Group allocation was performed after enrollment (i.e., after patients had provided written informed consent) via clustered block randomization, with a block consisting of 10 sequentially enrolled patients. To minimize the risk of communication between participants potentially influencing the outcomes, which can be a concern in settings like inpatient stays, the entire block was assigned to the same group. The sequence of all blocks was randomized before the start of the study based on a randomization list created in R. The last block of each group was truncated and ended as soon as the targeted sample size of n = 40 per group (not counting dropouts) was reached. The randomization list and the mode of randomization (clustered block randomization) were concealed from the blinded study assistant, who was responsible for recruiting and data collection, as well as from the clinical staff, to avoid unintended indirect influences from nurses or treating ward physicians. Only the study physician performing the ICP and LP according to the group allocation had the randomization list and was unblinded to group allocation.

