#### Main outcome: headache-related impairment

2.14.1

We hypothesize that headache-related impairment (main outcome) will be lower in the OPT group than in the SOC group during the main investigation period, assessed at three time points: 3 h (t3), 24 h (t4), and 72 h (t5) after LP. To test this hypothesis using a 2×3 mixed factorial study design, we will apply two-way repeated measures analysis of variance (ANOVA) to calculate an F-statistic on the main effect of the factor group (OPT vs. SOC) as well as the interaction effect between group and time point. The significance level (alpha level, type II error rate) for the probability over F (Pr(>F), *p*-value) will be set at 0.05. If *p* < 0.05, *post hoc* contrasts with correction for multiple comparisons (Bonferroni–Holm) will be performed. If the data do not meet assumptions of normality and homoscedasticity, we will instead use aligned rank transform ANOVA as the non-parametric alternative for the assessment of main effects and interactions (Wobbrock et al., 2011). The study will follow a per-protocol approach for the analysis.

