#### Secondary outcomes

2.14.2

Current, mean, and maximum headache intensity will be tested using two-way repeated measures ANOVA or the non-parametric alternative, in alignment with the analysis of the main outcome. The headache incidence and the use of on-demand pain medication will be used to calculate odds ratios to compare the odds of developing headaches or using pain medication up until 72 h after LP between the OPT and SOC groups. Differences in expectations regarding the extent of unwanted side effects, state anxiety, perceived warmth and competence of the physician, and satisfaction with the procedure will be assessed using independent t-tests or Wilcoxon rank-sum tests (in the case of non-parametric data). For confirmatory analyses of group differences in the secondary outcomes, an alpha level of 0.05 after comparison for multiple testing using the Bonferroni–Holm procedure will be regarded as statistically significant.

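### Two unordered F-tests at 0.05 serve one directional primary hypothesis, no result is named as confirming it, and the interaction does not test it

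*Protocol article*

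**What the plan says.** Section 2.14.1 of the protocol article gives the hypothesis: "headache-related impairment (main outcome) will be lower in the OPT group than in the SOC group during the main investigation period". To test it, the section specifies a 2×3 repeated measures ANOVA with F-statistics on "the main effect of the factor group (OPT vs. SOC) as well as the interaction effect between group and time point". One threshold of 0.05 is set for the p-value of the F-test, introduced as "The significance level (alpha level, type II error rate) for the probability over F". If p falls below 0.05, Bonferroni–Holm corrected contrasts follow. The text does not say whether that p belongs to the main effect, the interaction or either one, and it gives no order or split between them.

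Section 2.14.2 treats the secondary outcomes differently: "For confirmatory analyses of group differences in the secondary outcomes, an alpha level of 0.05 after comparison for multiple testing using the Bonferroni–Holm procedure" is the criterion there.

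Section 2.7 justifies the sample size on one of the two tests only: "With a power of 0.90, the study can detect an effect size f of at least 0.16 for the interaction effect". The analysis set is 80 patients, 40 per group (section 2.1).

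**The concern.** There are two linked problems.

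- **Success is not defined.** Two F-tests serve one hypothesis, each at 0.05, so a reader cannot tell in advance which pattern of results makes the trial positive. If either F suffices, the main claim carries more than the stated 5% risk. The secondary outcomes have a stated multiplicity rule; the pair of primary F-tests has none.
- **One of the two tests asks a different question.** The interaction asks whether the OPT–SOC difference changes over time. It has no direction and ignores the average difference. It can be significant when OPT is no better or is worse, and it has no power for a benefit of constant size. Yet it is the only test for which section 2.7 gives power.

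At stake is whether a claim that optimized communication lowers impairment rests on a test of that claim.

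**Working it through.** **Inputs from the protocol article:** N = 80, 40 per group (2.1); m = 3 time points (2.10.1); alpha 0.05 for the F-tests (2.14.1); power 0.90 at f = 0.16 for the interaction (2.7).

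**Assumptions not in the document:** correlation rho = 0.5 between time points, sphericity, normal data, independent patients. Ranges over rho are given where they matter.

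**1. Reproducing the stated power.** For the interaction, lambda = f²·N·m/(1 − rho) = 0.0256 × 80 × 3/0.5 = 12.29, with 2 and 156 degrees of freedom. Power is 0.885, and the f detectable at 90% power is 0.164, which rounds to 0.16. The protocol's figure reproduces under rho = 0.5. Over rho 0.3 to 0.8, interaction power at f = 0.16 runs from 0.75 to 0.999.

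**2. Two F-tests under the null.** The tests use separate error strata. If they are treated as independent, the chance of at least one significant F is 1 − 0.95² = 0.0975. Simulating the 2×3 ANOVA with 40 per arm gives 0.097 at rho 0.5 (100,000 runs), 0.098 at rho 0.8, and 0.093 with standard deviations of 1, 2 and 2 at the three times.

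**3. Error rate by success rule** (simulated, no true difference):

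| Rule for a positive trial | rho 0.5 | rho 0.8 |
|---|---|---|
| Either F significant | 0.097 | 0.098 |
| Main effect, or interaction plus a Holm-significant contrast | 0.058 | 0.054 |
| Any F plus a Holm-significant contrast favouring OPT | 0.018 | 0.017 |

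Section 2.14.1 states none of these rules.

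**4. What the interaction detects.** With n per group and d the OPT–SOC differences in SD units, centred on their mean, lambda = (n/2)·Σd²/(1 − rho). Negative differences favour OPT.

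- Differences 0, 0, +0.6 (OPT worse at 72 h only): centred −0.2, −0.2, +0.4, so Σd² = 0.24 and lambda = 20 × 0.24/0.5 = 9.6. The interaction is significant in 79% of simulated trials. In 78% it is significant with no Holm-adjusted contrast favouring OPT.
- Differences −0.4, 0, +0.4 (no average benefit): Σd² = 0.32 and lambda = 12.8. The interaction is significant in 90%, the main effect in 5%.
- Differences −0.6 at all three times (uniform benefit): Σd² = 0 and lambda = 0. The interaction is significant in 5%, the main effect in 90%.

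**5. Power of the main effect.** Here lambda = f²·N·m/(1 + (m − 1)·rho) = 0.0256 × 240/2 = 3.07, with 1 and 78 degrees of freedom. Power at f = 0.16 is 0.41 (0.49 at rho 0.3, 0.33 at rho 0.8). The f detectable at 90% power is 0.30, since 0.09 × 240/2 = 10.8. With two groups, f is half the standardized difference, so f = 0.30 is a uniform difference of 0.6 SD, in line with the 90% in step 4.

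**The case against.** The strongest reply is that a significant F is not itself a claim. It leads to Holm-corrected contrasts, the hypothesis has a direction, and an interaction driven by OPT being worse would show as such in those contrasts. Much of this stands. A reader might infer that the trial's false-positive rate simply is 9.75%, or that the plan would certify harm as benefit. The document supports neither: 9.75% needs the rule that either F alone is success, which the text does not state, and the contrasts would show direction. But the rules that would bring the rate to about 5–6% or 2% are not stated either.

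Reporting both effects is also routine for a mixed ANOVA. That is true of the output, but section 2.14.1 assigns both effects to the single hypothesis.

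A reader might add inflation from the allocation of whole blocks of ten patients (section 2.7). That is a separate question. The document gives no intracluster correlation, so no such figure belongs here.

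The type II label is a slip: the same phrase says alpha level and the value is 0.05, so no analysis changes.

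Finally, making the main effect the sole primary test demotes the only test for which the protocol gives power. That is correct and is a real cost.

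**Conclusion.** The concern holds as a missing success rule combined with a test that does not match the hypothesis. The false-positive rate of the primary claim lies between about 2% and about 9.75%, depending on a rule the protocol does not give; the upper figure applies only if either significant F counts as success. Whatever the rule, a significant interaction alone is not evidence that impairment was lower under OPT. The 79% and 5% figures assume rho = 0.5, normal data and independent patients. The qualitative point needs none of these, because a constant benefit contributes nothing to the interaction. These tests and this alpha are fixed in the protocol's own text, so this is not detail left to an analysis plan that is not shown.

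**What to change.** In section 2.14.1, name the group main effect (mean impairment over t3 to t5, OPT minus SOC) as the single primary test at two-sided 0.05, reported with an estimate and 95% confidence interval. Make the interaction and the Holm-adjusted time-point contrasts supportive. Correct the label to type I error rate.

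The edit to 2.14.1 is a few sentences, but it has two costs. A pure interaction can no longer make the trial positive. Section 2.7 must also be restated for the main effect: with N = 80 and an assumed correlation of 0.5, power at f = 0.16 is about 0.41 and the f detectable at 90% power is about 0.30. The article describes enrolment (December 2023 to May 2024) in the past tense, so a larger sample is unlikely to be an option.

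Keeping both tests at 0.025 each would hold the error at 1 − 0.975² = 0.0494, with power at f = 0.16 of 0.82 for the interaction and 0.30 for the main effect. It would still leave one of the two tests not addressing the hypothesis.

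The article describes the analysis as still to come. The rule should be fixed and dated before group comparisons are run; if results are already known, the ambiguity should be reported with them.

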Especially, when an invasive diagnostic procedure is planned, patients are routinely informed about relevant risks and potential complications before giving consent. The lumbar puncture (LP) is a particularly common diagnostic procedure in neurology, used to collect cerebrospinal fluid (CSF) from the spinal canal. Investigation of CSF is part of the basic workup of a plethora of neurological and neuropsychiatric symptoms and is often critical for the diagnosis of inflammatory processes of the nervous system (e.g., meningitis, encephalitis, multiple sclerosis, inflammatory neuropathies), subarachnoid hemorrhage, neurodegenerative diseases (e.g., Alzheimer’s disease), or oncological processes (e.g., meningeal carcinomatosis) (Jane and Wray, 2024). It involves inserting a needle into the subarachnoid space of the spinal canal at the lumbar level to passively drain CSF. A known potential side effect of this procedure is postdural puncture headache (PDPH) (Plewa and McAllister, 2024), which is thought to be caused by intracranial hypotension, resulting in strain on the meninges. Symptoms typically appear within 48–72 h and are usually, though not exclusively, orthostatic, that is, worsening when upright and improving when lying down (Plewa and McAllister, 2024). The incidence reported in the literature varies widely, ranging between 2 and 40%, but generally not exceeding 10% when atraumatic needles are used (Nath et al., 2018; Tumani et al., 2019; Plewa and McAllister, 2024). Given that lumbar puncture is a routine procedure, with thousands performed worldwide every day, any reduction of the burden of headaches due to nocebo effects is, therefore, likely to be impactful.

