#### Headache-related impairment

2.10.1

The main outcome is headache-related impairment, and was rated 3 h (t3), 24 h (t4), and 72 h (t5) after a lumbar puncture on a numerical rating scale (NRS) with integer values ranging from 0 (= no impairment) to 10 (maximum imaginable impairment). Patients were asked to rate their headache-related impairment since the lumbar puncture (t3) or since the last survey time point (t4, t5), respectively: “How severely have you felt impaired by headache since the lumbar puncture?” (original in German: “Wie stark fühlten Sie sich seit der Lumbalpunktion durch Kopfschmerzen beeinträchtigt?”). The construct of impairment was chosen as it allows/encourages the patient to integrate different dimensions of the individual negative pain experience (i.e., impact on activity, pain unpleasantness, pain intensity, duration) into his/her assessment.

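### The aligned rank transform fallback does not hold its 5% level on an impairment score that is mostly zeros; the size of the excess depends on a zero share the protocol does not state

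*Protocol article*

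**What the plan says.** The primary outcome is rated at 3 h, 24 h and 72 h on a scale with "integer values ranging from 0 (= no impairment) to 10 (maximum imaginable impairment" (section 2.10.1). Section 2.14.1 fixes the analysis: "To test this hypothesis using a 2×3 mixed factorial study design", a two-way repeated-measures ANOVA tests the group effect and the group-by-time interaction, each at 0.05. (The text calls 0.05 a type II error rate; I read it as type I.) The switch is conditional: "If the data do not meet assumptions of normality and homoscedasticity", then "we will instead use aligned rank transform ANOVA as the non-parametric alternative for the assessment of main effects and interactions". Section 2.14.2 extends the rule: "Current, mean, and maximum headache intensity will be tested using two-way repeated measures ANOVA or the non-parametric alternative".

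The expected share of zero ratings is not given. These statements bear on it:
- Introduction: the incidence of postdural puncture headache is "generally not exceeding 10% when atraumatic needles are used". Section 2.9 says only atraumatic needles were used.
- Introduction: in a cited 28-patient study, 47% of informed and 8% of uninformed patients had a headache.
- Section 2.4: patients with chronic headache, or with headache as the main reason for admission or puncture, are excluded.

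**The concern.** If most ratings are exactly 0, normality fails and the fallback becomes the primary test in practice. Aligned rank transform ANOVA is built for responses with few ties. On a score with a large block of identical zeros, it can turn chance differences between cell means into systematic rank differences. The only primary outcome, and three headache-intensity outcomes, would then be tested by a method that rejects too often when the two ways of communicating are equivalent. The rule would also leave a test that holds its level on such data for one that does not.

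**Working it through.** **1. The plan's own figure.** Section 2.7 gives a detectable effect of f = 0.16 at power 0.90 for the interaction. With the usual G*Power defaults (correlation 0.5, sphericity 1; assumed, not stated), λ = f²·N·m/(1−ρ) = 0.0256 × 80 × 3 / 0.5 = 12.29 on 2 and 156 df. Power is 0.885, and f for power 0.90 is 0.164, which rounds to 0.16. The figure is reproduced. It describes the ordinary ANOVA and says nothing about the error rate of the fallback.

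**2. Will the fallback be triggered?** Even the highest headache rate cited, 47%, leaves 100 − 47 = 53% of patients at 0 throughout. The 10% figure would leave about 90%. A score with most values on its lower bound does not meet normality.

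**3. Why alignment fails.** Write m_gt for the mean in group g at time t, m_g. and m_.t for the margins, and m.. for the grand mean. The aligned value is the cell residual plus the estimated effect. For a patient scoring 0 it becomes:
- group effect: 0 − m_gt + (m_g. − m..) = m_g. − m_gt − m..
- interaction: 0 − m_gt + (m_gt − m_g. − m_.t + m..) = m.. − m_g. − m_.t

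Identical zeros therefore take a different value in each group-by-time cell, set only by chance differences in means. Ranking turns these small gaps into large separated blocks of ranks. Patients in one group who score 0 at all three times also share the same three ranks, so they add almost nothing to the error term against which the group difference is judged.

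**4. Size under the null.** Both arms are drawn from the same distribution: 40 per arm, 3 time points, integer 0–10 with a point mass at 0, latent within-patient correlation 0.5. Scores are aligned, ranked with midranks, and analysed by split-plot ANOVA on 1, 78 and 2, 156 df. Each scenario has 2,000 to 10,000 simulated trials; ranges span repeated runs.

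| Affected per time point (assumed) | Aligned ranks, group | Aligned ranks, interaction | Either test |
|---|---|---|---|
| 10% | 50–53% | 36–37% | 67–68% |
| 20% | 30–32% | 22–23% | 41–44% |
| 30% | 18–20% | 14–17% | 28–31% |
| 40% | 12–14% | 10–11% | 19–20% |
| 50% | 8–10% | 8% | 15–17% |
| 60% | 7% | about 6% | about 13% |

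On the same data ordinary repeated-measures ANOVA and ANOVA on unaligned midranks each reject in 4–6% per test. Either-test rates must be set against about 9–11% for ordinary ANOVA, since two tests at 5% already give 1 − 0.95² = 9.75% if independent.

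**5. Where the cited 47% falls.** In this model 20% affected per time point corresponds to 39% affected at any time, and 30% to 53%. A cumulative 47% lies between, so the group-test error lies between the 30% and 20% rows, about 18% to 32%.

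**6. Robustness.** Over correlations 0.3–0.9 and two shapes for the positive scores, the group error runs from 10–14% at 60% zeros to 45–54% at 90% zeros. With incidence varying over time (10-20-15%, 20-35-25%, 30-45-40%) it is 9–37%, and the interaction error reaches about 41%. If 60–90% of patients are 0 throughout, the group error is 12–46% and the interaction error 24–46%. On continuous normal data the same code gives 4.3–5.2%, so the inflation is not a coding error.

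**The case against.** The strongest reply is that the size is not known. A reader might infer that the primary test has a 13–50% false-positive rate outright. The documents do not support that. The 10% figure is for postdural puncture headache, whereas the outcome asks about impairment from any headache; episodic headache is not excluded, and every patient in this trial is informed of the risk. The 47% figure is nearer to the outcome, though it comes from 15 informed patients. If half or more are affected at each time point, the group test is off by only a few points. This weakens the 50% end but not the direction.

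Three further inferences go too far. Comparing the either-test rate with 5% mixes the defect with ordinary two-test multiplicity; the right comparator is about 9–11%. Calling a significant result uninterpretable overstates the harm: the aligned-rank p-value would be unreliable, but section 2.13 commits to sharing data and code, and a valid re-test would be possible. And the defect does not require a block-level permutation test in place of the whole analysis. That would drop the interaction on which sections 2.7 and 2.14.1 rely. It would also bring in the allocation of whole blocks of ten patients, which is a separate issue and is ignored in these simulations.

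One technical limit stands: the procedure was coded from its definition, and the R package for it was not run.

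**Conclusion.** The point holds in conditional form. The fallback fixed in section 2.14.1, and carried to headache intensity in section 2.14.2, is unsuitable for a bounded integer score with many tied zeros. With 40 per arm and correlation 0.5, the group test's false-positive rate is about 7–10% with 50–60% affected per time point, 13% with 40%, 18–20% with 30%, about 31% with 20% and about 50% with 10%. The interaction test runs at about 6–36% over the same range. At least one of the two is significant in about 13–69% of null trials across the runs, against about 9–11% for ordinary ANOVA.

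This rests on an assumed zero share, which the article's headache figures and exclusions make likely to exceed one half, and on the normality check then triggering the switch. The cause is the alignment step, because unaligned ranks hold their level on the same data.

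**What to change.** By a dated amendment made before unblinded analysis, delete the aligned-rank fallback for headache-related impairment and for current, mean and maximum headache intensity. Keep the planned repeated-measures ANOVA for the group and group-by-time effects whatever the normality check shows. As sensitivity analysis, name a method that does not align before ranking: ANOVA on plain midranks, or, for the group effect, a rank or permutation test on each patient's mean score over t3–t5.

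The hypotheses, the sample size and the basis of the power statement stay as they are. The programming cost is small. The real cost is a documented and justified change to a preregistered analysis after recruitment, which should state that it was made without sight of results by group.
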